# Spread and scale of an electronic deprescribing software to improve health outcomes of older adults living in nursing homes: study protocol for a stepped wedge cluster randomized trial

**DOI:** 10.1186/s13063-021-05729-0

**Published:** 2021-11-02

**Keywords:** Polypharmacy, Deprescribing, Older adults, Long-term care, Medication use, Medication review, Adverse drug event, Nursing home, Prescription check-up

## Abstract

**Background:**

Medication overload or problematic polypharmacy is a major problem causing widespread harm, particularly to older adults. Taking multiple medications increases the risk of potentially inappropriate medications (PIMs), and residents in long-term care (LTC) are frequently prescribed 10 or more medications at once. One strategy to address this problem is for the physician and/or pharmacist to perform regular medication reviews; however, this process can be complicated and time-consuming. With a prescription review, medications may be decreased, changed, or stopped altogether. MedReviewRx is a software that runs an analysis using deprescribing rules to produce a report to guide medication reviews addressing medication overload for residents in LTC.

**Methods:**

This study will employ a mixed methods effectiveness-implementation hybrid type 2 study design. To measure effectiveness, a stepped wedge cluster randomized trial design is planned, which allows us to approximate a randomized clinical trial. Approximately 1000 residents living in LTC will be recruited from five facilities in New Brunswick. The study will begin with 3 months of baseline data on rates of deprescribing. Thereafter, every 3 months a new cluster will enter the intervention mode. The intervention consists of medication reviews augmented with the MedReviewRx software, which will be used by staff and clinicians in the facilities. The estimated study duration is 18 months and the main outcome will be the proportion of patients with one or more PIMs deprescribed (reduced/stopped or changed to a safer alternative) in the 90 days following a prescription review. The goal is to study the impact of MedReviewRx on medication overload among older adults living in LTC. In typical fashion of a stepped wedge cluster randomized trial, each cluster acts as an internal control (before and after) as well as a control for the other clusters (external control). Qualitative data collected will include resident/caregiver attitudes towards deprescribing and semi-structured interviews with staff working in the long-term care homes.

**Discussion:**

This study design addresses issues with seasonality and allows all clusters to participate in the intervention, which is an advantage when the intervention is related to quality improvement. This study will provide valuable information on PIM use, cost savings, and facilitators and challenges associated with medication reviews and deprescribing. This study represents an important step towards understanding and promoting tools to guide safe and rational reduction of PIM use among older adults.

**Trial registration:**

NCT04762303, Registered February 21, 2021.

## Administrative information

Note: the numbers in curly brackets in this protocol refer to SPIRIT checklist item numbers. The order of the items has been modified to group similar items (see http://www.equator-network.org/reporting-guidelines/spirit-2013-statement-defining-standard-protocol-items-for-clinical-trials/).

## Background and rationale (6a)

As highlighted by the Working Group on Medication Overload [1], problematic polypharmacy is an overwhelming problem for older adults. Nearly two thirds of community-dwelling adults are taking five or more medications [2] and while most medications are prescribed to help people live longer, healthier lives, the more complex a medication regimen is, the more dangerous it becomes. With each added drug, the risk of an adverse drug event (ADE) increases [3], as well as the worsening of geriatric syndromes [4]. A growing body of evidence suggests that patients and physicians may not recognize ADEs and additional new medications may be prescribed to treat an existing ADE [5]. This so-called prescribing cascade further increases polypharmacy and the risk of ADEs. Aging itself is a risk factor for ADEs as changes in organ function, body weight, fat distribution, cognition, balance, function, and drug receptor sensitivity all affect medication metabolism and side effects [6]. Experts in geriatrics have published guidelines and lists of medications to be avoided or used cautiously in older adults [7–9]. These medications are often referred to as potentially inappropriate medications or PIMs. PIMs are medications associated with a high risk of ADEs when administered to older adults and may be of uncertain or no clinical benefit [10]. Continued use of PIMs in later life further increases the risk of ADEs associated with polypharmacy in older adults. Furthermore, as highlighted in a 2018 systematic review, there is a significant association between an increased number of medications and frailty, which is associated with an increased risk of adverse events in older adults [11].

Older adults living in nursing homes are at a particularly high risk of polypharmacy and ADEs as they are frail and often take ten or more medications [2]. Some of these medications increase the risk of falls, fractures, kidney injury, bleeding, and death. Costs to the healthcare system from polypharmacy are very high and stem from emergency department visits, hospital admissions, and direct and indirect drug costs. As such, strategies to address polypharmacy are needed. One approach is the process of deprescribing, whereby a prescriber or pharmacist establishes the full list of medications a patient is taking and contextualizes them for the individual patient [12]. Based on the medical history, a measure of frailty, and the patient and/or caregiver’s values or preferences, safer classes of medications are selected, doses may be decreased, and medication may be discontinued [12]. This process can be thought of as a “prescription check-up.”

While deprescribing may be effective for stopping PIMs, manually reviewing all drugs and cross referencing them with patient conditions and lists of inappropriate drugs in older adults requires an expert command of the literature and is time-consuming. In many Canadian provinces, nursing home medication reviews are mandatory; however, there are no consistent guidelines for the reviews and therefore existing processes often result in medications being re-prescribed without documentation of a clear rationale or reassessment. Studies in acute care hospitals have demonstrated that electronic decision support can facilitate the process of deprescribing and augment the proportion of patients with one or more PIM (potentially inappropriate or problematic) medications stopped upon discharge from the hospital [13]. More studies looking at electronic tools for deprescribing in nursing homes are needed to determine if an investment on the part of the government into a software that supports deprescribing is warranted.

An electronic decision support tool for deprescribing called MedSafer has been studied in the Canadian acute care context. MedSafer augmented the proportion of patients who were discharged from the hospital with one or more PIMs deprescribed as compared to usual care [13]. New Brunswick (NB) has the highest proportion of older adults compared to other provinces in Canada. In NB, 20.8% of the population is over 65 years of age and this is expected to increase to 31.3% by the year 2038 [14]. Strategies to promote regular prescription check-up are needed to reduce polypharmacy in the setting of LTC. For this study, MedSafer researchers partnered with the Centre for Innovation and Research in Aging (CIRA) at York Care Centre (YCC) to improve a previously developed web-based application (polypharmacy app) that allowed prescribers in New Brunswick Nursing Homes (NBNHs) to visualize MedSafer deprescribing reports on a desktop computer or tablet. The polypharmacy app, called MedReviewRx, will be implemented in a number of NBNHs.

### Research questions

What is the impact of the MedReviewRx App on deprescribing PIMs in NBNHs (effectiveness)?Is the MedReviewRx App developed at YCC, in Fredericton NB, feasible (easy to use), does it provide useful information, and does it reduce the time needed to conduct a medication review in other NBNHs?How often do nursing home health care providers log into the MedReviewRx App, and how often does this action result in a prescription check-up (review and deemed appropriate or review and medication change)?What are the challenges to implementing the MedReviewRx App in other NBNHs and what improvements are required for widespread use of the MedReviewRx App?

### Objectives [7]

To embed software enabled deprescribing in five NBNHs using MedReviewRx, an App containing MedSafer recommendations, in order to study the effectiveness at deprescribing PIMs, measured at the individual resident level.

To test the feasibility (ease of use) of implementing electronic deprescribing in LTC homes measured at the individual prescriber level.

### Trial design [8]

This is a hybrid type 2 effectiveness-implementation design for quality improvement research that will make use of mixed methods of evaluation. Implementation consists of using MedReviewRx. Effectiveness analysis consists of measuring the impact of the MedReviewRx on PIMs. Exploratory surveys (the mixed methods component of the study) which look at qualitative and quantitative user feedback and patient and caregiver attitudes about deprescribing will be used to explain study findings. Informal feedback, surveys and semi-structured interviews will be used to examine user experience with MedReviewRx. The Revised Patient Attitude Towards Deprescribing (rPATD) questionnaire “older adult” version for the patients and a “caregiver” version for family members/substitute decision makers will be used to describe patient and family member attitudes about deprescribing medications.

### Intervention description {11a}

Estimated study duration is 18 months, and the effectiveness component of the study will use a deployment strategy which approximates a stepped wedge cluster randomized trial (SW-CRT). This design has many advantages and is considered the most robust type of study design for pragmatic quality improvement interventions. Each cluster will contribute a control period. Subsequently, at each of 3 pre-defined time periods, one cluster will be randomly assigned to transition from control to intervention. In this way, all clusters act as an internal control (before and after) as well as a contemporaneous control for the other clusters (external control). The study is composed of three clusters and each cluster contains the following number of beds: Cluster A 218, Cluster B 314, and Cluster C 272.

InterRAI Long-Term Care Facilities (LTCF) assessments are standardized for nursing home residents. These assessments are used to help identify health issues among residents, develop care plans, and monitor changes in the health of LTC residents. InterRAI LTCF assessments are conducted quarterly for every person living in a nursing home in New Brunswick. These assessments contain sociodemographic information, medical diagnoses, information on medications used by the resident, and variables which describe cognitive and physical function. The interRAI LTCF assessment form is completed by gathering input from the care team and responses are inputted electronically into Momentum Healthware (Momentum) software by nurses or interRAI coordinators.

MedSafer is a computer program which cross-references medical conditions, ICD-10 diagnosis codes, and medication drug identification numbers (DINs) to generate a deprescribing opportunities report that can be used by the prescriber as a roadmap for a comprehensive prescription check-up.

The MedReviewRx system uses an application programming interface (API) to communicate with MedSafer. Patient assessments are downloaded from Momentum and uploaded into MedReviewRx at the nursing home. MedReviewRx removes identifiable patient information and assigns a unique identifier to each person’s data set, and anonymized data sets are encrypted and securely transmitted to MedSafer for analysis. MedSafer analysis is securely transmitted back to MedReviewRx where it is linked to the appropriate patient file and is available to be viewed by nursing home prescribers during their regular medication review. MedSafer deprescribing reports list medication(s) which have been flagged as potentially inappropriate, why the medication may be inappropriate, tapering instructions and links to patient and family materials if available. Figures 1 and 2 provide sample screenshots of the application.

**Fig. 1 Fig1:**
[figure not shown]
Sample screenshot of MedReviewRx App

**Fig. 2 Fig2:**
[figure not shown]
Sample screenshots of MedReviewRx App

### Criteria for discontinuing or modifying allocated interventions {11b}

There is no planned interim analysis as the intervention is considered safe and best practice. The study will be analyzed according to the intention to treat principle.

### Strategies to improve adherence to interventions {11c}

We will provide training for the software users, along with memos and email remainders about the study during the intervention phase. Ultimately, the decision to use the software will up to the individual prescriber as this is a pragmatic intervention to study the real-world effectiveness of making the software available for use in the LTC homes.

### Relevant concomitant care permitted or prohibited during the trial {11d}

All usual care received by the participant is allowed to continue during the trial.

### Provisions for post-trial care {30}

Participants in the trial will continue to receive usual care in the LTC home post-trial completion.

### Sample size {14}

Based on the Canadian Institute for Health Information’s report, titled “Drug Use Among Seniors in Canada, 2016”, we expect that about 70% will be taking one or more PIMs. This yields an average cluster size of 175 for patients with at least 1 PIM. Uptake of deprescribing using the MedSafer report in acute care studies ranges from 8 to 25% [13] over usual care. Conservatively, we think we can increase the proportion of patients with 1 or more PIM deprescribed from a baseline rate of 10 to 20% (absolute increase of 10% or a number needed to treat of 10). Using the Shiny CRT calculator [15], we estimate that we will have at least 72% power to detect this difference under assumptions of cluster autocorrelation of 0.8 and a within period intra-cluster correlation (ICC) 0.05. This increases to 96% power if the ICC is 0.02.

### Recruitment {15}

Nursing homes may experience 20 to 30% patient turnover each year due to deaths; therefore, the total number of nursing home residents who have at least one interRAI LTCF assessment during the study period is approximately 1000. For the purposes of analysis, only the initial closed cohort will be included in the study. New residents will not be analyzed in the current study. All homes have agreed to participate in the study and an individual waiver of consent has been granted by the Horizon Health Network Research Ethics Board.

### Sequence generation {16a}

Computer-generated random numbers were used in order to generate the allocation sequence of the clusters.

### Concealment mechanism {16b}

Study sites are not aware of which clusters they are assigned to and will only be made aware that they are entering into intervention mode approximately 4 weeks prior, to allow for training on the use of the software.

### Implementation {16c}

The principal investigator ([name]) of the study generated the allocation sequence. Participants are automatically enrolled in the study and assigned to the intervention when the targeted nursing homes agree to take part in the study.

### Who will be blinded {17a}

The study investigators and analyst will be blinded to the intervention status at the time of outcome adjudication. Prescribers cannot be blinded as the intervention is the use of a computer software.

### Procedure for unblinding if needed {17b}

There is no procedure for unblinding (does not apply to the trial design).

### Plans for assessment and collection of outcomes {18a}

Each study site will appoint a site contact to load information into MedReviewRx and to communicate with the study team. The nursing home site contact or designate(s) will be emailed a Nursing Home Site Assessment Questionnaire for completion prior to project implementation. The purpose of this questionnaire is to determine information about the nursing home including workflow, structure of medication reviews, physician, pharmacy, and nursing support. This information will be used to inform implementation and determine where MedReviewRx fits into the workflow. Study sites will also receive an implementation toolkit containing a user manual, instructions on how to use the Momentum extract report, a research study PowerPoint presentation, template for Staff/Crew Meeting “huddles”, sample announcement of study frequently asked questions, and a list of deprescribing resource websites. The CIRA research manager or designate will review the Nursing Home Site Assessment Questionnaire and Toolkit resources with the study site contact. If a nursing home site is not completing section N1 (list of all medications) of the interRAI LTCF assessment, a research assistant will be trained to enter this information for the study site.

The study will begin with a minimum 3-month control phase. During the control phase, MedReviewRx will not be accessible to healthcare professionals at the nursing homes. This serves to obtain baseline deprescribing levels for each nursing home. Every 3 months thereafter, a cluster of nursing homes will enter intervention mode.

During the control phase, nursing home residents and their families or substitute decision makers will be recruited to complete a survey to explore patient attitudes about deprescribing in this NB study population. The rPATD questionnaire “older adult” version will be provided to nursing home residents and the “caregiver” version will be provided to family members and substitute decision makers. Survey questions will be entered in Lime survey to promote electronic completion whenever possible. A recruitment poster will be displayed at study sites and a recruitment communication will be sent to family members and substitute decision makers identified in the resident’s admission package. Paper copies will also be available from the study site contact. Residents and family members who ask nursing home staff about the survey will have their contact information forwarded to the CIRA research manager to answer questions and obtain verbal consent to have a survey emailed to them. If email is not available, a research assistant will contact the participant to administer the survey over the phone. Study site contacts may also distribute paper copies of the surveys if requested and permitted by the study site.

During the control phase, health care providers and study site staff will be recruited to register for MedReviewRx. A recruitment communication will be sent by email and placed in study site mailboxes. Study recruitment will also be encouraged at interdisciplinary nursing home meetings such as Pharmacy and Therapeutics and Medical Advisory Committee meetings. User training will be provided by the study site contact or designate as determined by the site-specific implementation plan. Nursing home site contacts will participate in an interview to evaluate MedReviewRx implementation. Implementation interviews will be conducted within the first 3 months of the site intervention phase.

During the intervention phase, MedReviewRx will be made available to nursing homes with the understanding that it will be used to facilitate medication reviews and prescription check-ups. MedReviewRx (see Figs. 1 and 2 for screenshots of the App) provides clinicians with access to individualized and prioritized deprescribing information from MedSafer which:
A)Identifies PIMs.B)Explains why the medication is potentially inappropriate.C)Provides instructions on how to safely stop/taper the medication.D)Links to patient informational brochures with non-pharmacologic interventions and rationale for deprescribing from the Canadian Deprescribing Network

Nursing homes will also have the option to print MedSafer deprescribing reports from MedReviewRx for clinicians who do not have computer access or who choose not to register to use MedReviewRx. If reports are printed, they will be placed in a binder for the prescriber to sign and date indicating that they have read the report. Prescribers and nursing home staff will be encouraged to write feedback directly on the report if they wish too. To assess the proportion of reports that were read, and feedback provided on the reports, signed reports will be kept in a locked cabinet for research assistants to collect. If visitor restrictions are in place, the study site contact will gather signed reports, place them in a sealed envelope(s), and send them to the CIRA research manager using a courier method that can be tracked and requires a sending signature and signature of receipt.

Clinicians will review deprescribing opportunities (electronically or via a paper report) and determine if medications can be tapered or stopped. Medication changes are discussed with the resident or substitute decision maker as part of usual care. This process will not change with the implementation of MedReviewRx. If the prescriber decides to alter a medication based on the deprescribing opportunities provided by MedSafer and their expert knowledge, the prescriber will do so in the same manner as they did prior to implementation of MedReviewRx, and discussion with the resident and/or substitute decision maker will occur according to the process in place at each nursing home.

During the intervention phase, an analysis of deprescribing opportunities will be conducted by MedSafer once every 3 months for each resident in the nursing home. Results will be stored in the MedReviewRx system to be accessed at any time.

Patients who die or are hospitalized will be censored from the study.

MedReviewRx has been designed to have Administrator accounts and Clinician accounts which restrict access according to user function. Study site contacts (or site designate) will load data into MedReviewRx using the Administrator function. Prescribers (physicians and nurse practitioners) and pharmacists will be provided with Clinician accounts. Clinicians will only access MedReviewRx records for patients under their care. MedReviewRx registration has been designed to restrict nursing home staff access to residents at their site only. Prescriber and pharmacist access will be restricted to study sites where they practice. MedReviewRx access will be audited by the CIRA research manager or designate.

User feedback on MedReviewRx and MedSafer deprescribing information will be solicited from prescribers, pharmacists, and nursing home staff throughout the study using surveys. Surveys may be completed via Lime Survey, on paper or by telephone. Three surveys will be distributed by email to registered MedReviewRx users as well as other study site prescribers, pharmacists, and nurses who may have access to printed reports from MedReviewRx. Paper copies of the surveys will also be available at the study site nursing units. A MedReviewRx user feedback survey will be distributed at the end of the first and third quarter of the intervention and an acceptability and feasibility survey will be distributed at the end of the study. Paper copies of completed surveys will be collected by the study site contact, placed in a sealed envelope(s), and sent to the CIRA research manager using a courier method that can be tracked and requires a sending signature and signature of receipt. Courier costs will be paid for by CIRA. MedReviewRx users will be provided with a study email which they may use to submit feedback and questions at any time throughout the study. Informal feedback received by email from users will be reviewed and actioned by the CIRA research manager or designate. Email feedback will be documented anonymously in an excel spreadsheet and reported to the study principal investigators within 1 week of receipt to determine if tasks need to be submitted to the technical team for software updates. Rapid cycle improvements in usability of the system and MedSafer output will be made based on survey results and informal feedback.

Informal feedback written on printed MedSafer reports will be documented in an excel spreadsheet and included in the analysis of qualitative feedback provided by survey and interview.

Frequency of MedReviewRx use will be measured electronically by counting the number of times a user accesses their account.

Overall experience with the research project will be evaluated using semi-structured interviews conducted at the end of the intervention period.

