#### Impact on PIMs

The impact on PIMs will be determined by the proportion of nursing home residents who have one or more PIMs reduced or stopped after the treating physician receives a MedSafer report. This outcome will be measured by using unique identifiers to compare medication data from sequential interRAI data sets. PIMs identified in the baseline data set will be compared with the next data set (3 months later) transmitted with that unique identifier to determine if any of the PIMs has been stopped (no longer listed) or if a PIM dose has been reduced. This process will continue for the study duration. All statistical comparison will be performed via STAT v 15 (or equivalent) and the stepped wedge function will be used for the primary outcome (proportion of patients with one or more PIMs deprescribed over the study period).

At the end of the study, subgroup analysis will be conducted on the PIM data to explore PIM use based on sex, gender, and geographic location.

Co-primary outcome:
User experience with MedSafer reports and MedReviewRx.

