#### User experience

User experience with MedSafer reports and MedReviewRx will be measured using survey responses as well as described through interview data and informal feedback received by the study team. Several outcomes will be studied: how satisfied the user is with the App, including how helpful they find it, the added knowledge from a MedSafer report for the prescriber, how likely the prescriber is to continue using the App once the study is over. Survey responses will be analyzed based on the following themes: value and benefits, scientific content, and user satisfaction. Interview data will be thematically analyzed [16].

Secondary outcomes to be examined at 90 days following each intervention cycle include:
A)Although we are not powered to show a reduction in other outcomes, we will explore any impact of the intervention on reduction of fractures, falls, use of restraints, transfer to hospital, change in functional status (based on interRAI activities of daily living (ADL) scores), episodes of delirium (based on responses to questions in Section C of the interRAI LTCF assessment form: periodic disordered thinking or awareness) and death.

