#### Materials

Electronic documentation of medications and medical conditions in Momentum interRAI LTCF assessment software.MedSafer software system for identifying PIMs.A secure Cloud Service to store information. This will be obtained through a subscription from Canadian Web Hosting.MedReviewRx, a system which extracts, de-identifies, and transmits data between study nursing homes and MedSafer and provides an interface for viewing MedSafer outputs on mobile devices and computers.Nursing Home Assessment QuestionnaireImplementation ToolkitUser Feedback SurveyAcceptability and Feasibility SurveyrPATD questionnaire “older adult” version for the patients and a “caregiver” version for family members and substitute decision makers.Recruitment materials

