### Adverse event reporting and harms {22}

We do not expect reports to contain errors. MedSafer has already been extensively tested on older adults with polypharmacy in the acute care setting (up to one third of whom were from the long-term care setting). If a clinician suspects that a report contains an erroneous recommendation, they are encouraged to email the study team for support. The study email is monitored daily during regular business hours.

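### MedSafer output may be revised during the trial while MedSafer also identifies the PIMs scored as the primary outcome; one frozen rule version should score every quarter

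*Protocol article*

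**What the plan says.** The sentence at issue is in the protocol article, Plans for assessment and collection of outcomes {18a}: "Rapid cycle improvements in usability of the system and MedSafer output will be made based on survey results and informal feedback". The same section sends emailed feedback to the principal investigators "to determine if tasks need to be submitted to the technical team for software updates", and it schedules the surveys: "A MedReviewRx user feedback survey will be distributed at the end of the first and third quarter of the intervention".

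The feedback is not confined to the look of the tool. Under User experience, survey answers are analysed by the themes "value and benefits, scientific content, and user satisfaction". Under Adverse event reporting and harms {22}: "If a clinician suspects that a report contains an erroneous recommendation, they are encouraged to email the study team for support".

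MedSafer also has a measuring role. Materials lists it as the "MedSafer software system for identifying PIMs", and the inclusion criteria require at least one PIM flagged by it. The outcome is built quarter by quarter under Impact on PIMs: "PIMs identified in the baseline data set will be compared with the next data set (3 months later) transmitted with that unique identifier". A PIM counts as deprescribed if it has left the medication list or its dose has fallen, and the comparison is repeated throughout the study.

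Section {18a} describes the three-monthly MedSafer analysis of each resident for the intervention phase. The article does not say when, or with which version, PIMs are identified in control-quarter data.

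**The concern.** The same software delivers the intervention and fixes which drugs can score. Adapting the intervention is normal in a hybrid effectiveness-implementation trial. Letting the outcome definition move with it is a separate matter, and the two can be kept apart.

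Suppose feedback leads to a rule being added. Residents then have more drugs at risk of being recorded as deprescribed, and the outcome proportion rises even if prescribers behave as before. A withdrawn rule works the other way. If old and new versions are divided between control and intervention cells, that change is read as an intervention effect, positive or negative.

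**Working it through.** **Inputs**

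- Base rate 10%, target 20%, average cluster size 175, cluster autocorrelation 0.8, ICC 0.05 or 0.02: Sample size {14}.
- Three clusters and four quarters, with 0, 1, 2 and 3 clusters in intervention mode in turn: Participant timeline {13}.
- Time and intervention as fixed effects, cluster as a random effect, logit link: Statistical methods {20a}.
- Assumed, not in the article: no true effect; PIMs act independently; a relative change *x* in flagged PIMs per resident.

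**Step 1. The plan's own figures.** The article gives no figure for this point. Its power statement (72% at ICC 0.05, 96% at ICC 0.02) was used only to check the layout. Generalised least squares on cluster-quarter means, with two-sided alpha 0.05 (assumed) and variance (0.09 + 0.16)/2 = 0.125, gives 56.9% and 78.1% for a cross-sectional design. For a closed cohort with an assumed individual autocorrelation of 0.8 it gives 70.4% and 95.7%, close to the stated values. This point does not dispute the power statement.

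**Step 2. Shift in the outcome from a rule change alone.** With a 10% base rate, P(at least one PIM deprescribed) = 1 − 0.9^(1+x).

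| Change in flags | Proportion | Shift (points) |
|---|---|---|
| +10% | 10.9% | +0.9 |
| +25% | 12.3% | +2.3 |
| +50% | 14.6% | +4.6 |
| −25% | 7.6% | −2.4 |
| −50% | 5.1% | −4.9 |

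To mimic the whole 10-to-20% effect, 1 + x = ln 0.8 / ln 0.9 = 2.118. That is about 112% more flags.

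**Step 3. How much of the shift reaches the treatment estimate.** This was worked on the risk-difference scale for simplicity; the article's model uses a logit link.

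- *The new version scores all clusters from a given quarter on.* Every cell in a quarter moves equally, so the period effect takes it up. Spurious effect: 0.
- *The new version scores all intervention cells and no control cells.* The shift coincides with the treatment indicator. Spurious effect for +10%, +25%, +50%: +0.9, +2.3, +4.6 points.
- *The new version scores only intervention cells from the third quarter.* The one intervention cell left out is the first cluster in quarter 2. After removing cluster and quarter means, its treatment indicator is 1 − 3/4 − 1/3 + 1/2 = 5/12. The squared residuals over all 12 cells sum to 10/12. Its weight is therefore 1/2, and half the shift remains: +0.5, +1.2, +2.3 points.
- *One frozen version scores every cell.* Spurious effect: 0.

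**Step 4. Can versions differ between cells of one quarter?** The article does not say that they will. The gap is that MedSafer runs are described for intervention quarters only, so control data could be scored at another time. Explanation for the choice of comparators {6b} also has assessments downloaded in batches by assessment date, so an update could fall between batches.

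**The case against.** **The sentence may concern usability only.** It can be parsed as usability of the system and usability of the output, and elsewhere the article uses output for the displayed report. A survey theme on scientific content and an invitation to email about suspected errors do not say that rules will be edited. This stands: a rule change is permitted by the wording, not announced.

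**Time is in the model.** A reader might infer that bias follows simply because later quarters contain more intervention time. The documents do not support that. Time is a fixed effect, MedSafer is one program reached through one interface, and an update reaching all clusters together is absorbed (Step 3, first case).

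**A withdrawn rule is not a stopped drug.** A reader might infer that un-flagging a drug would be scored as deprescribing. Impact on PIMs compares medication data, and a dose reduction can be seen only there. On the natural reading, a dropped flag does not count as a stop. What remains is the choice of drugs followed: "PIMs identified in the baseline data set will be compared with the next data set".

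**The cohort is closed.** Recruitment {15} limits the analysis to the initial cohort, so the documents do not support a drifting population as a main source of error.

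**Opportunity is limited.** Participant timeline {13} puts the feedback survey in months 4–6 and 10–12, and the last intervention quarter ends at month 12. At most one scheduled round can feed in-trial changes, besides emails.

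**Scoring versions could be left to the full protocol or SAP.** In general that is fair. Here, however, the article itself announces changes to the output of the program that identifies the outcome events.

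**Conclusion.** The point holds in conditional form. Two things must both occur: the improvements reach the PIM rules, and control and intervention cells are scored by different versions. The article establishes neither and excludes neither. If both occur, the outcome definition differs by arm. The spurious effect is then about 0.9, 2.3 or 4.6 points for 10%, 25% or 50% more flags, half that if only intervention cells from the third quarter are affected, and of opposite sign if flags are removed. These sizes rest on assumed flag changes, independent PIMs, a 10% base rate and no true effect; they are not forecasts. Set against a 10-point target and a stated 72% power at ICC 0.05, they justify a change that costs almost nothing. They do not show that the planned analysis is biased.

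**What to change.** For the analysis, identify PIMs in every stored data set, for all clusters and all control and intervention quarters, with one MedSafer rule version frozen before the first cluster switches. Keep judging stops and dose reductions from the medication data, as Impact on PIMs indicates. Log the date of every version released to sites. The live application may keep improving.

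State in section {18a} whether the planned improvements concern usability only or may also alter the PIM rules. If usability only, that sentence settles the matter.

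The cost is one batch re-run of stored, de-identified data sets. The one small drawback is that the scored PIM list may differ slightly from what clinicians saw late in the trial.
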